#### Secondary outcome measures

Clinical outcomes to be used in the large RCT include the following:I.Health-related quality of lifeII.Diet qualityIII.Physical activityIV.Hand-grip strengthV.WeightVI.Body compositionVII.Shape-up evaluation questionnaireVIII.Healthcare services use2.Willingness of clinical staff to recruit participants will be assessed with a short one-to-one interview with the clinicians at the beginning of the third month of recruitment.3.The number and type of potential adverse effects of the intervention will be recorded during the intervention and at the follow-up interview (for example, gastro-intestinal complaints from a change in diet).4.Costs relevant to recruitment, screening, implementation, and follow-up will be calculated. We will also measure retrospectively the healthcare resource use and cost them at national rates.5.Reasons for non-participation and loss to follow-up will be tracked for each participant lost and merged in similar categories.6.At 8 and 24 weeks follow-up, a purposive sample (30 %) of participants in each arm will be interviewed to assess their experience of participating in the trial, the acceptability of the intervention and the materials, and their overall experience of the program, including potential facilitators or barriers to adherence. All participants who may dropout will also be approached for an interview. These data will help with the refinement of the intervention.

### Participant timeline

Figure 1 demonstrates the flow chart of the study. Table 2 shows the assessments at each time point.

**Fig. 1 Fig1:**
[figure not shown]
Flow-chart

**Table 2 Tab2:** Study assessments at specific time points

			Study Period				
	Staff member	Pre-study screening/consent	Baseline	Allocation	Post-allocation		
Time point			Week -3	Week 0	Week 1	Week 8	Week 24
ENROLMENT							
Eligibility screen	Interviewer	X					
Informed consent	Interviewer	X					
Allocation	Study Coordinator			X			
INTERVENTIONS							
Shape-up	Interviewer						
Usual care	Interviewer						
ASSESSMENTS							
Socio-demographic data	Interviewer		X				
EORTC-QLQ-C30	Interviewer		X			X	X
EORTC-QLQ-EN34	Interviewer		X			X	X
Dietary assessment	Interviewer		X			X	X
Physical activity	Interviewer		X			X	X
Weight	Interviewer		X			X	X
Height	Interviewer		X				
Body composition	Interviewer		X			X	X
Waist circumference	Interviewer		X			X	X
Hand-grip strength	Interviewer		X			X	X
Blood pressure	Interviewer		X			X	X
Shape Up evaluation	Interviewer					*X* ^2^	*X* ^2^
Control group input	Interviewer						X^3^
Qualitative interviews	Interviewer					X	X
Health care resource use	Interviewer						X
EQ5D-3 L	Interviewer		X			X	X
Serious adverse report form	Study Coordinator	As needed throughout the protocol					

^1^Closeout for the control group will be at week 40 after receiving the intervention

^2^Only the intervention group

^3^Only in the control group

### Sample size

Although this is a feasibility study, a sample size has been specified for examining the recruitment rate, using A’Hern’s approach for one-stage phase II trials [48]. Regarding recruitment, a success rate of approximately 30 % or more would be desirable for the trial to be considered feasible. A success rate of 15 % or less would be unacceptable. The trial will test the null hypothesis H_0_ that recruitment is ≤ 15 % against the alternative hypothesis H_1_ that recruitment is ≥ 30 %. With a 5 % level of significance and 90 % power, 64 participants are needed so that we can estimate whether the percentage of participants with successful recruitment is ≤ 15 % or ≥ 30 %. If we can recruit 15 or more participants, we can reject the null hypothesis.

A trial of 64 (32 per arm) will be sufficient to test the above hypothesis and allow decisions to proceed to a Phase III trial. It will also allow for rich feedback from the participants to be used for the optimisation of the procedures and the materials. Lastly, it will allow a certain degree of precision in calculating standard deviations for the secondary outcomes that will be the key design parameters for the main study [49].

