### Study setting

Participants will be recruited from two major academic hospitals in London with sufficient caseload of endometrial cancer patients; University College London Hospitals NHS Foundation Trust, and Barts Health NHS Foundation Trust. The intervention program will be delivered at the University College Hospital Macmillan Cancer Support and Information Centre, located in central London.

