### Outcome measures

#### Primary outcome measures

The primary outcome measures for the pilot trial are as follows:The recruitment rate.The adherence rate (attendance of the sessions).The retention rate (complete follow-up).

The main criterion to judge the pilot study successful and a large-scale RCT feasible using the recruitment measure is recruiting (consenting) 30 % of the eligible participants (32 participants per 110 estimated to be eligible in each centre during the 6-month recruitment). This target seems reasonable based on our previous experience and similar rates indicated in the literature [46, 47]. The primary measure to be used in the large-scale RCT is projected to be a change in global quality of life as measured by the EORTC Quality of Life Questionnaire (QLQ-C-30). However, the choice of additional primary outcomes will be finalised after taking into account the results of the feasibility study.

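### The recruitment cut-off of 15 is valid only for 64 eligible women observed, but the protocol uses 64 as the number enrolled from about 220 eligible

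*Protocol article*

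**What the plan says.** The Sample size section sets up the recruitment test "using A’Hern’s approach for one-stage phase II trials". The hypotheses are "H_0_ that recruitment is ≤ 15 % against the alternative hypothesis H_1_ that recruitment is ≥ 30" %. It continues: "With a 5 % level of significance and 90 % power, 64 participants are needed", and gives the decision rule as "If we can recruit 15 or more participants, we can reject the null hypothesis". The next paragraph carries the figure over to the trial itself: "A trial of 64 (32 per arm) will be sufficient to test the above hypothesis".

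Two other places in the article set a recruitment criterion.

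- Primary outcome measures gives the main criterion for success as "recruiting (consenting) 30 % of the eligible participants (32 participants per 110 estimated to be eligible in each centre during the 6-month recruitment").
- Statistical methods asks that the lower 95% confidence limit for recruitment be at least 15%.

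The Recruitment section plans on 1.07 participants per week per hospital for 30 weeks, and Study setting names two hospitals. The Abstract also gives 64 as the number of participants.

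**The concern.** In a one-stage design of this kind, n counts the units on which success or failure is observed, and the cut-off counts the successes. For a recruitment rate the unit is an eligible woman and success is her consent. Women who have been enrolled and randomised have all consented, so they form the numerator of the rate and cannot be its denominator.

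The Sample size section uses 64 in both roles. If 64 is the number enrolled, the cut-off of 15 is attached to the wrong total, and the stated 5% level and 90% power do not describe the test this trial would carry out. Recruitment is a primary outcome, and the section says the test will support the decision on a Phase III trial. A cut-off that is far too lenient for its denominator should therefore not stand. It also follows that the recruitment test gives no reason to enrol 64.

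**Working it through.** **Inputs**

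- Null rate 15%, alternative 30%, level 5%, power 90%, n = 64, cut-off 15 (Sample size).
- Eligible women: 110 per centre (Primary outcome measures) × 2 centres (Study setting) = 220.
- Consents expected: 32 per centre × 2 = 64, and 64/220 = 29.1%. The weekly rate agrees: 1.07 × 30 × 2 = 64.2 (Recruitment).
- Retention test: n = 62, cut-off 44, 60% against 75%, level 5%, power 80% (Statistical methods).

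**Step 1. Reproduce the plan's figure.** With X binomial(n, p), alpha = P(X ≥ r | n, 0.15) and power = P(X ≥ r | n, 0.30).

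- P(X ≥ 15 | 64, 0.15) = 0.0491
- P(X ≥ 15 | 64, 0.30) = 0.9026

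A search for the smallest n that meets one-sided 5% and 90% power returns n = 64, r = 15. A one-sided 2.5% level would give n = 79, r = 19, so the plan used one-sided 5%. The arithmetic is correct for 64 eligible women observed.

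**Step 2. Apply the cut-off to the protocol's own denominator of 220.**

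- 15/220 = 6.8%, exact (Clopper-Pearson) 95% CI 3.9% to 11.0%. The whole interval lies below 15%, and 15% of 220 is 33 women.

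| True recruitment rate | P(X ≥ 15), n = 220 |
|---|---|
| 15% (the null) | 0.9999 |
| 10% | 0.960 |
| 7% | 0.580 |

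The figure of 220 is an estimate. Over an assumed range of 180 to 260 eligible women, the probability at a true 15% is 0.997 or more throughout.

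**Step 3. Compare the three recruitment rules, all at 220 eligible.**

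| Section | Rule | Consents needed of 220 | Does 15 pass? |
|---|---|---|---|
| Sample size | 15 or more | 15 | Yes |
| Statistical methods | Lower 95% limit ≥ 15% (exact, two-sided) | 45 | No (limit 3.9%) |
| Primary outcome measures | 30% of eligible | 64 (2 × 32) to 66 (0.30 × 220) | No (6.8%) |

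**Step 4. Cut-offs that fit 220.**

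| Cut-off | Rate | One-sided alpha at 15% | Power at 30% | Exact two-sided 95% lower limit | Exact one-sided 95% lower limit |
|---|---|---|---|---|---|
| 43 | 19.5% | 0.040 | 0.9998 | 14.5% | 15.2% |
| 45 | 20.5% | 0.018 | 0.9995 | 15.3% | 16.1% |

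The smallest cut-off with one-sided alpha of at most 5% is 43 (42 gives 0.058). It misses the 15% target if the limit is two-sided and meets it if the limit is one-sided. The smallest cut-off that meets the two-sided target is 45 (44 gives 14.9%).

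**Step 5. Check that 64 enrolled can be justified otherwise.** P(X ≥ 44 | 62, 0.60) = 0.049 and P(X ≥ 44 | 62, 0.75) = 0.812. The retention test reproduces and needs 62 participants, so 64 covers it.

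**The case against.** A reader might infer that the protocol would declare the pilot feasible at about 7% recruitment. The document does not support that. The main criterion, in Primary outcome measures, is 30% of eligible women and has the right denominator. Statistical methods adds the confidence-limit target. Fifteen of 220 fails both. The Sample size section says that 15 allows the null hypothesis to be rejected; it does not say that the pilot then succeeds, and the Discussion foresees four graded conclusions. So the cut-off of 15 is one of three conflicting recruitment rules and not the sole rule.

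There is also a coherent reading of the test paragraph taken alone. It speaks of a percentage of participants successfully recruited, which makes sense only if the 64 are women assessed, and on that reading 15 of 64 is a correct rule. This moves the slip to the next paragraph, where 64 becomes two arms of 32, but does not remove it. On that reading the recruitment test gives no basis for a trial of 64.

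Finally, the enrolment target itself is not in doubt. It agrees with the expected consents per centre and with the weekly rate, and if 64 of 220 consent (exact 95% CI 23.2% to 35.6%) the null is rejected under any of the cut-offs above.

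**Conclusion.** The point holds as an error of unit, not of arithmetic. The design with n = 64 and cut-off 15 is correctly computed for 64 eligible women, but the protocol uses 64 as the number randomised and expects those 64 from about 220 eligible. Applied to 220, the stated cut-off corresponds to a rate of 6.8% and has a type I error of about 0.9999 at a true 15%, where the plan claims 5%. It contradicts the protocol's other two recruitment criteria, and the article does not say which of the three governs.

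This rests on the protocol's estimate of 110 eligible women per centre and on independent binomial outcomes. The conclusion does not depend on the exact count: it is the same across the assumed range of 180 to 260.

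**What to change.** 1. State in Sample size that the denominator of the recruitment test is the eligible women, about 220 by the protocol's estimate.
2. Replace the cut-off of 15 with one for the number of eligible women actually observed, chosen to agree with the confidence-limit target in Statistical methods. For 220 this is at least 45 consents. A cut-off of 43 can be used only if that target is restated as a one-sided 95% limit.
3. Restate the error rates to match: one-sided alpha 0.018 and power above 0.999 at 30% for 45 of 220, or alpha 0.040 for 43 of 220.
4. Say how the test relates to the 30% criterion in Primary outcome measures, so that a single set of recruitment rules remains.
5. Drop the claim that the recruitment test requires 64 enrolled women. Justify the 64 by the retention test (62 needed) and by the precision of the standard deviations, which the protocol already cites.

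The cost is a rewording of these sections and one recalculated cut-off. No extra patients are needed.

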### Recruitment

Potential participants will be recruited from outpatient clinics at the two hospitals. They will be identified and approached by a member of the clinical team. Bright colour reminders will be attached at the cover of the patient notes before their appointment to enhance consultants’ engagement with recruitment. After initial screening from the clinician, and if the patient is willing to hear about the study, following verbal consent, the patient will be introduced to the researcher attending the clinic for final screening and a detailed discussion of the study. All participants will need to consent for themselves following standard procedures (Additional file 3). We expect to recruit on average 1.07 participants per week per hospital during the 30-week recruitment period to reach our target.

The clinical teams in the two hospitals will also identify potential participants who have been treated in the two recruitment sites but have been followed up at local sites. Following the General Practitioner’s verification that the participants are alive, invitation letters signed by the consultant will be sent to these women, along with the participant information sheet, an opt-in form, the barriers to participation survey [50], and a business reply envelope.

### Data collection, management and analysis

#### Data collection methods

Participants will visit the laboratory for three 90-min one-to-one assessments. They will complete the widely used, reliable and validated European Organization for Research and Treatment of Cancer Quality of Life Questionnaire (QLQ-C30) [54] and Endometrial Cancer Module (QLQ-EN24) [55]. We will use the Stanford 7-Day Physical Activity Recall [56], a 15-min interview-based tool, to assess physical activity, which has shown acceptable reliability and validity [57] and is responsive to change.

Dietary intake will be assessed with one weekday 24-hour dietary recall using the ASA24 web-based tool [58]. Nutrition and statistical software will be used to calculate how well the participant’s diet fits to recommended healthy eating patterns. Our previous piloting of the assessment indicated acceptability and feasibility. Diet quality will be calculated by the Alternative Healthy Eating Index (AHEI) score, assessing how well a diet fits to recommended healthy eating patterns and being a strong predictor of survival [59]. An updated version of the DINE questionnaire [60], together with questions about fruits and vegetables, will supplement the 24-hour dietary recall data.

Weight to the nearest 0.1 kg and body composition will be assessed using MC980 multi-frequency segmental body composition analyser. Using standardised protocols, standing height will be assessed to the nearest 0.1 cm, and handgrip strength, using a handgrip dynamometer. Waist circumference will be measured to the nearest 0.1 cm [61]. Blood pressure will be measured using an automated sphygmomanometer with the participant seated comfortably for 5 minutes before measurement and the arm supported at the level of the heart. All measurements will be taken twice and averaged for analysis. Participants will also complete six socio-demographic questions. Researchers will be receiving standardised training with all measurements.

Participants will also complete the *Shape-up* questionnaire at all time points; ten items in a five-point Likert scale (from ‘Strongly disagree’ to ‘Strongly agree’) that reflect the overall goals of the programme (for example, I am in control of my food portion sizes, I can set effective eating and activity goals and work towards them). At the end of the program, the intervention-arm participants will be given an 18-item evaluation form [62] to complete at home and return by post. At the 24-week follow-up, the control arm will complete two more questions assessing the input about diet and physical activity they received from external sources, to allow an assessment of contamination. At the last follow-up, all participants will also complete a healthcare resource using a six-item questionnaire [63]. Quality-of-life adjusted years (QALYs) will be assessed with the validated six-item EQ5D-3 L [64].

After they have taken enough time to decide about their participation, individuals will be asked their reason(s) for non-participation [50]. The same questions and prompts will be asked of participants who decide to withdraw from the study. Participants may withdraw from the study for any reason at any time. However, we will make every reasonable effort to follow the participants for the entire study period. If a follow-up appointment in the laboratory is not possible after three consecutive contact attempts, a researcher will request to visit the participants at home for the interview or undertake this by telephone. Participants will not be aware of this option beforehand to maximise the chances for having the physical measurements.

### Data management

This study has been registered for Data Protection at UCL Records Office (Reference: Z6364106/2014/12/14). Standard procedures following Data Protection Act 1998, the NHS Code of Confidentiality, and Good Clinical Practice will be implemented throughout the study.

### Statistical methods

In addition to recruitment rate, the study is also examining adherence rate and retention rate (complete follow-up). Adherence is defined as the proportion of engaged participants attending at least one of the last three sessions of the intervention. Engaged participants are those who have attended at least two sessions of the intervention. Best practice guidance suggests that programmes should be commissioned if at least 60 % of participants are likely to adhere [37]. A success rate approximately of 85 % or more would be desirable. That means that 85 % or more of the engaged participants in the intervention group will attend at least one of the last three sessions of the intervention. A success rate of 60 % or less would be unacceptable. The trial will test the null hypothesis H_0_ that adherence is ≤ 60 % against the alternative hypothesis H_1_ that adherence is ≥ 85 %. With a 5 % level of significance and 90 % power, 27 participants are needed so that we can estimate whether the percentage of participants with successful adherence is ≤ 60 % or ≥ 85 %. If 21 or more participants have a successful adherence, we can reject the null hypothesis.

Regarding retention (attendance of both follow-up sessions) rate, a success rate of approximately 75 % or more would be desirable. A success rate of 60 % or less would be unacceptable. The trial will test the null hypothesis H_0_ that complete follow-up is ≤ 60 % against the alternative hypothesis H_1_ that complete follow-up is ≥ 75 %. With a 5 % level of significance and 80 % power, 62 participants are needed so that we can estimate whether the percentage of participants with complete follow-up is ≤ 60 % or ≥ 75 %. If 44 or more participants have a complete follow-up, we can reject the null hypothesis.

Recruitment, adherence and retention rates will be reported as proportions with 95 % CIs. The target lower 95 % confidence limit for the following outcomes are 15 % or more, 60 % or more, and 60 % or more for recruitment, adherence, and retention, respectively.

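### The success counts follow one-sided 5% tests, but the confidence-limit targets for the same outcomes state neither sidedness nor which criterion decides

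*Protocol article*

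**What the plan says.** The protocol article gives two numerical criteria for each of its three primary outcomes.

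**Success counts.** Sample size designs the recruitment test "using A’Hern’s approach for one-stage phase II trials", with an unacceptable rate of 15% or less, a desirable rate of 30% or more, 5% significance and 90% power. This gives n = 64 and the rule "If we can recruit 15 or more participants, we can reject the null hypothesis". Statistical methods adds two tests of the same form:
- Adherence: 60% against 85%, 5% significance, 90% power, n = 27: "If 21 or more participants have a successful adherence, we can reject the null hypothesis".
- Retention: 60% against 75%, 5% significance, 80% power, n = 62: "If 44 or more participants have a complete follow-up, we can reject the null hypothesis".

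**Confidence-limit targets.** Statistical methods then says that the three rates will be reported with 95% confidence intervals. The next sentence sets targets for the lower 95% "confidence limit for the following outcomes are 15"% or more for recruitment, and 60% or more for both adherence and retention.

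The article does not say whether the target limit is one-sided or two-sided, names no interval method, and does not say whether the count or the limit decides. The later sentence setting 5% significance for the primary outcomes is also silent on sidedness.

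**The concern.** The null and alternative hypotheses are directional, so a 5% exact test puts all 5% in one tail. A conventional 95% confidence interval puts 2.5% in each tail, so requiring its lower end to reach the null value amounts to testing at one-sided 2.5%. That is a stricter rule than the one that produced the counts.

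The targets come straight after the sentence announcing 95% intervals, so the natural reading is that they refer to the lower end of those intervals. A result exactly at a cut-off could then pass the test and miss the target. The Sample size section says the trial is meant to support a decision on a Phase III trial, and the Discussion lists four possible verdicts on feasibility. If the governing criterion is chosen only once the results are known, the prespecification of these primary outcomes is weakened. If the two-sided limit governs, the stated power no longer applies to the rule in use.

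**Working it through.** **Inputs** (Sample size for recruitment; Statistical methods for the other two). Write p0 for the unacceptable rate, p1 for the desirable rate and r for the success count.
- Recruitment: n = 64, r = 15, p0 = 0.15, p1 = 0.30
- Adherence: n = 27, r = 21, p0 = 0.60, p1 = 0.85
- Retention: n = 62, r = 44, p0 = 0.60, p1 = 0.75

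**Step 1: reproduce the stated designs.** With X binomial(n, p), one-sided alpha = P(X ≥ r | p0) and power = P(X ≥ r | p1).
- 15/64: alpha 0.0491, power 0.9026
- 21/27: alpha 0.0421, power 0.9014
- 44/62: alpha 0.0492, power 0.8121

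Each is the smallest exact design at one-sided 5% with the stated power. The counts are correct, and they are one-sided 5% rules.

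**Step 2: lower limits at the stated counts.** The exact (Clopper-Pearson) lower limit for k successes is the a-quantile of Beta(k, n − k + 1), with a = 0.025 for a two-sided 95% interval and a = 0.05 for a one-sided 95% limit.

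| Lower limit | 15/64 (target 15%) | 21/27 (target 60%) | 44/62 (target 60%) |
|---|---|---|---|
| Two-sided 95%, exact | 13.75% | 57.74% | 58.05% |
| Two-sided 95%, Wilson | 14.75% | 59.24% | 58.71% |
| Two-sided 95%, Agresti-Coull | 14.65% | 58.90% | 58.65% |
| Two-sided 95%, Jeffreys | 14.38% | 59.81% | 58.91% |
| Two-sided 95%, mid-P | 14.28% | 59.39% | 58.80% |
| Two-sided 95%, Wald | 13.06% | 62.10% | 59.67% |
| One-sided 95%, exact | 15.04% | 60.79% | 60.05% |

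Every two-sided limit misses its target except Wald for adherence: 0.7778 − 1.96 × √(0.7778 × 0.2222 / 27) = 0.621. The exact one-sided limit meets all three targets. With one success fewer (14, 20, 43) it gives 13.74%, 56.77% and 58.35%, and misses all three. The one-sided exact limit is therefore the same rule as the counts.

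**Step 3: counts needed if the two-sided limit decides**, at the same denominators.
- Recruitment: 16/64 (exact limit 15.02%), alpha 0.0248, power 84.4%
- Adherence: 22/27 (exact limit 61.92%), alpha 0.0155, power 79.0%
- Retention: 46/62 (exact limit 61.50%), alpha 0.0140, power 62.4%. 45/62 just misses at 59.77%. With Wilson limits 45/62 is enough (60.41%), alpha 0.0272, power 72.6%.

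The smallest exact designs that keep the stated power at one-sided 2.5% are 19/79, 25/32 and 57/80.

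**Step 4: how often the two rules would disagree.** With exact limits they disagree only at 15 (recruitment), 21 (adherence), and 44 or 45 (retention). If the true rates equal the desirable rates, the probabilities are the differences in power between the two rules:
- Recruitment: 0.9026 − 0.8438 = 0.059
- Adherence: 0.9014 − 0.7903 = 0.111
- Retention: 0.8121 − 0.6238 = 0.188

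**The case against.** The strongest reply is that there is no contradiction. The counterpart of a one-sided 5% exact test is a one-sided 95% lower limit, the targets equal the three null boundaries, and on that reading the limits reproduce 15, 21 and 44 exactly. The authors may simply have restated their tests in interval form. This stands as a possible reading and rules out calling the conflict proven. It does not remove the ambiguity, because the article never states this reading and the preceding sentence points the other way.

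Three further points limit the size.
- **Method.** The article names no interval method, which an article may properly leave to a fuller document. A reader might infer that the limits miss at every cut-off whatever the method. They do not, since Wald clears the adherence target. It still misses the other two.
- **Denominators.** A reader might infer that the trial will in fact have only 84%, 79% and 62% power. Those figures hold for exact limits at n = 64, 27 and 62. Primary outcome measures expresses recruitment against about 110 eligible women per centre, or 220 in all. On 220, the exact two-sided target is met from 45 recruits, with power 99.9% at a true rate of 30%. If all 32 intervention participants are engaged, both exact rules require 25/32 for adherence, and there is no gap. With all 64 in the retention denominator, the rules differ by one participant (46 against 47).
- **Consequence.** The Discussion allows graded verdicts, and the limits are called targets, not overriding rules. It would go too far to say that the two criteria must produce opposite feasibility verdicts.

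All three stand as limits on the size. None says which criterion decides.

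**Conclusion.** The concern holds as unstated sidedness together with an unstated order of precedence between two criteria for the same primary outcomes. If the target is the lower end of a two-sided 95% interval, which is the natural reading in context, exact and score-type limits at 15/64, 21/27 and 44/62 fall short of 15%, 60% and 60%, by 1.25, 2.3 and 1.95 percentage points for the exact limit. If it is a one-sided 95% limit, the criteria agree and nothing else changes.

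The practical effect is confined to one count for recruitment, one for adherence and one or two for retention. At the desirable rates and with exact limits, the chance of landing there is about 6%, 11% and 19%. These figures, and the power of about 84%, 79% and 62% (73% for retention with Wilson), assume the planning denominators. The stated counts, sample sizes and power are correct for the one-sided 5% tests. This should be fixed, but it does not undermine the design.

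**What to change.** Add one sentence to Statistical methods: the target refers to the exact one-sided 95% lower confidence limit, which is the lower end of the two-sided 90% interval; it is equivalent to the success counts at the planning denominators; and two-sided 95% intervals are reported for description only. At the stated counts this limit is 15.04%, 60.8% and 60.05%, so counts, sample size and power all stay as they are.

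If the two-sided 95% limit is meant to decide, name the interval method and restate the rules. With exact limits at the planning denominators these are 16/64, 22/27 and 46/62, with power of about 84%, 79% and 62%. With Wilson limits, retention becomes 45/62, with power of about 73%.

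In either case, say which criterion decides, and do so before the outcome data are seen. The first option costs one sentence, with no extra participants or data. The second also needs no more participants, unless the stated power is to be kept, which would take 19/79, 25/32 and 57/80.
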